## 6. Study duration and phasing

Based on the sample size considerations above the total study duration will be 8 months. Ideally the 14 units would move from the baseline to the intervention on a 2-weekly basis, but this is impractical. Therefore, they will change on a monthly basis in pairs. Simulations by Moulton et al for a similar study design showed that the effect of pair-wise stepped implementation on the DEFFsw was minimal.

Introduction of the GeneXpert as a replacement of sputum smear examination, i.e. moving a unit from the baseline to the intervention group, will be scheduled for a fixed date; the change will be implemented overnight. In the months prior to this date the necessary preparations for the change will be made, including installation of the GeneXpert equipment, delivery of test kits, training of staff, dry run of the assay, and instructions of the staff in the clinics that will request smear examinations.

Below is a graphic representation of the study timeline (by month).

|  | 1 | 2 | 3 | 4 | 5 | 6 | 7 | 8 | 9 | 10 | 11 | 12 | 13 |
| --- | --- | --- | --- | --- | --- | --- | --- | --- | --- | --- | --- | --- | --- |
| Ethical approval | x |  |  |  |  |  |  |  |  |  |  |  |  |
| Visit of all sub sites | x |  |  |  |  |  |  |  |  |  |  |  |  |
| SOP elaboration | x | x |  |  |  |  |  |  |  |  |  |  |  |
| Machine importation |  | x |  |  |  |  |  |  |  |  |  |  |  |
| Staff training |  |  | x |  |  |  |  |  |  |  |  |  |  |
| Observation period |  |  |  | x | x | x | x |  |  |  |  |  |  |
| Linkage of databases and extraction of data |  |  |  |  |  |  |  | x | x | x |  |  |  |
| Data analysis |  |  |  |  |  |  |  |  |  | x | x |  |  |
| Report and scientific paper writing |  |  |  |  |  |  |  |  |  |  |  | x | x |

## 7. In- and exclusion criteria

Since this study aims to assess the impact of introduction of a new diagnostic tool in routine practice, the no in- and exclusion criteria will be introduced in addition to the routine in- and exclusion criteria for diagnosis of TB in the Brazilian health system. According to the current NTP guidelines, every respiratory symptomatic (cough for more than 3 weeks) should be submitted to sputum examination. Likewise, all TB suspect (fever, weight loss, suggestive chest radiograph) will be submitted to examination of spontaneous or induced sputum or bronchoalveolar lavage. This examination will be AFB smear during the observation period and Xpert during the intervention period.

## 8. Data collection

The main study will make use of routinely collected data using two nationwide implemented reporting systems:

1. The TB reporting system. This is part of the nationwide notification system of infectious diseases, SINAN. In this system, notification of TB is mandatory.[[24]](#footnote-2)
2. The laboratory reporting system. The Brazilian Ministry of Health is currently implementing a nationwide laboratory reporting system, GAL. Positive TB testing results of smear examination and culture, as well as of anti-TB drug susceptibility testing, are entered on-line in the system by the diagnosing laboratory. The system will allow for inclusion of positive GeneXpert results.

Both systems will be aligned so that records can be linked on at the individual patient level, using *Reclink*.[[25]](#endnote-25) The variables name, mother’s name, age, neighborhood of residence, date of sputum collection, date of beginning of treatment will be used for linkage. Linkage will allow to detect slightly different writings of the same name (such as accents, “h”), and the other variables will be used to confirm the subject. Thereby a comparison of the GAL and the SINAN system will identify cases that have been diagnosed but not notified. Once data have been extracted, all identification fiels will be excluded from the study database, and all information will be treated anonymously.

## 9. Laboratory methods

Smear examinations, cultures and drug susceptibility testing will be done as per routine. The GeneXpert will be introduced as a routine laboratory procedure and performed in accordance with the manufacturer’s instructions (http://www.cepheid.com) and guidelines drawn based on the validation study that is currently ongoing. No additional laboratory testing will be done. No attempts will be made by the study to interfere with routine laboratorial procedures. Likewise, the routine clinical management will be the same, according to the clinician’s judgment, the NTP guidelines and the good clinical practices.

## 10. Data management and analysis

Over the end of the observation period, data from Manaus and Rio will be extracted from SINAN and GAL as described above. The routine procedures to check errors and linkage will be performed by the designated units in the Health Department, as per routine. This procedure includes checking for duplication, suspected incompatibilities, scale errors. Units are then informed. In Rio, [name] is responsible for this routine. In Manaus, by the municipal TCP manager, [name]. Once this procedure and linkage is done, the identification variables will be deleted and the following variables will be retained for analysis:

- From both SINAN and GAL: patient code, age, sex, health district of residence, sputum smear and culture resultsError: Reference source not found
- From SINAN only: clinic of notification, diagnostic classification (smear-positive/smear-negative/extrapulmonary), treatment history (new, previously treated), date of diagnosis, date of treatment initiation, HIV status, other major co-morbidities.
- From GAL only: positive sputum smear examination details (number of positive smears, highest smear grade obtained, date(s), laboratory); positive mycobacterial culture (number of positive cultures, identification, date(s), laboratory); drug susceptibility results (DST done yes/no, results for each drug tested, date(s), laboratory); positive GeneXpert (number of assays done; highest value obtained; rifampicin resistance yes/no/indeterminate, date(s), laboratory).

General data cleaning will be performed, including checks for duplicate entries, suspected mismatches, range errors, and results communicated to the responsible surveillance units for updating.

The patient code will be assigned for the analysis only and have no reference to patient identifiers.

The data analysis will be performed using STATA and will include:

- 1. Calculation of the number of diagnosed, bacteriologically confirmed pulmonary TB cases by smear status, for each unit, separately for baseline and intervention period.
  2. Calculation of the number of notified pulmonary TB cases, irrespective of bacteriological confirmation, by smear status and in various strata of age, sex and HIV status, for each unit, separately for baseline and intervention period.
  3. Calculation of the number of notified, bacteriologically confirmed pulmonary TB cases by smear status and in various strata of age, sex and HIV status, for each unit, separately for baseline and intervention period.
  4. Calculation of rates for each of these three, by dividing the numbers summed over all units and strata by the summed population denominators, separately for baseline and intervention period, with their 95% confidence intervals, and calculation of the rate ratios and rate differences comparing the two periods with appropriate significance testing.
  5. Multivariate analysis of the observed rate ratios using Poisson regression to adjust for potential confounding due to unbalanced randomization by age, sex, history of TB treatment, HIV status (as far as available), unit and month of enrollment.
  6. Similar calculation of numbers, rates, rate ratios and rate differences by HIV status (as far as available).
  7. Calculation of proportion of diagnosed pulmonary TB patients who are ultimately diagnosed as having MDR-TB, by smear status at initial diagnosis, for each unit, separately for baseline and intervention period.
  8. Calculation of the risk ratios and risk differences for these proportions comparing the two periods with appropriate significance testing.
  9. Multivariate analysis of the observed risk ratios using logistic or log-linear regression (as appropriate, depending on observed proportions) to adjust for potential confounding due to unbalanced randomization by age, sex, history of TB treatment, HIV status (as far as available), unit and month of enrollment.
  10. Calculation, for patients ultimately identified with MDR-TB, of the time interval between diagnosis of pulmonary TB and detection of rifampicin resistance, by smear status at initial diagnosis, for each unit, separately for baseline and intervention period.
  11. Calculation, for patients ultimately identified with MDR-TB, of the time interval between diagnosis of pulmonary TB and initiation of second-line treatment, by smear status at initial diagnosis, for each unit, separately for baseline and intervention period.
  12. Calculation of differences for these time intervals comparing the two periods with appropriate significance testing.
  13. Multivariate analysis of the observed differences in these time intervals using linear to adjust for potential confounding due to unbalanced randomization by age, sex, history of TB treatment, HIV status (as far as available), unit and month of enrollment.

Details of data management will be specified in SOPs. Details of data analyses will be specified in a data analysis plan.

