As it will be afore detailed, the present rollout study proposes a change in the laboratory routine, not in the primary care health units (PCU). Randomization and data analysis will not be individual, but by laboratory/PCU. There is consistent evidence that this change will bring benefits to patients and their contacts, since an early bacteriologically confirmed diagnosis is foreseen, with consequent reduction in transmission. It is expected that this study will provide the NTCP with information for decision making regarding implementation of the technology, necessary personnel training, impact of the test in PCU and laboratory routines and other operational information.

In addition to the increased detection rate, secondary benefits from the substitution of GeneXpert for smears are expected, such as reduction of diagnosis delay of sensitive and drug-resistant TB, of morbidity, mortality and transmission. The reduction in the time to diagnosis of MDR-TB will allow the early treatment with second-line drugs recommended in these cases, also reducing morbidity and mortality, offering less opportunity for MDR-TB transmission. Finally, a reduction in the number of cases erroneously treated as TB is expected. Thus, this project ultimately intends to contribute to TB control in the country.

We emphasize that the present protocol includes only the operational pilot implementation study, other protocol submissions will follow for cost-effectiveness and acceptability studies. The validation study, previously submitted, was approved by CONEP and should be started in March 2011.

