| 2. Study design The design will be a group-based comparison with phased introduction of the GeneXpert (*stepped-wedge* or *phased implementation* design).[[22]](#endnote-23) The units of comparison will be defined as smear examination laboratories together with the clinics that drain upon them for this laboratory service, as defined above. A group-wise comparison is preferred because the intervention will be introduced at the group level (i.e. in laboratories) and the impact of the intervention is thus best assessed at the group level as well. Also, designs with individual comparisons (e.g. individual randomization) will disrupt clinic and laboratory routine and therefore introduce artificial elements that may bias the outcomes (Hawthorne effect).  In this design, all units will start in the *baseline* group, i.e. diagnose TB following current procedures. Each unit will then at different points in time change to the *intervention* group i.e. do GeneXpert instead of smear examination, such that at the end of the observation period all units will be in the intervention group. The sequence by which the units move from baseline to intervention will be randomized. In that way all units will contribute to the person-time observation of both the baseline and the intervention group, but with different durations. This will allow before-after comparison while taking account of potential bias that would be introduced if e.g. case detection rates change over time for reasons not related to the intervention.  See figure 1 for graphic explanation of the design.  *Figure 1. Graphic representation of study design.* | | | | | | | | | |
| --- | --- | --- | --- | --- | --- | --- | --- | --- | --- |
| **Time** | month 1 | month 2 | month 3 | month 4 | month 5 | month 6 | month 7 | month 8 |  |
| **Unit** |  |  |  |  |  |  |  |  |  |
| 1 |  |  |  |  |  |  |  |  |  |
| 2 |  |  |  |  |  |  |  |  |  |
| 3 |  |  |  |  |  |  |  |  |  |
| 4 |  |  |  |  |  |  |  |  |  |
| 5 |  |  |  |  |  |  |  |  |  |
| 6 |  |  |  |  |  |  |  |  |  |
| 7 |  |  |  |  |  |  |  |  |  |
| 8 |  |  |  |  |  |  |  |  |  |
| 9 |  |  |  |  |  |  |  |  |  |
| 10 |  |  |  |  |  |  |  |  |  |
| 11 |  |  |  |  |  |  |  |  |  |
| 12 |  |  |  |  |  |  |  |  |  |
| 13 |  |  |  |  |  |  |  |  |  |
| 14 |  |  |  |  |  |  |  |  |  |
|  | | | | | | | | | |
|  |  | baseline | |  | intervention | |  |  |  |

*Randomization procedure*

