## 5. Sample size

Since the study will done in two preselected municipalities and the distribution and number of TB microscopy services in these municipalities is largely predefined by the routine health care conditions under which we wish to observe the impact of a new diagnostic tool, the number of units for this study is fixed at 14. Since also the expected baseline TB notification rate for these units is fixed, the effective sample size can only be varied by varying the observation period.

Sample size calculations were based on the following principles and assumptions:

- Units serve a population of on average 500,000 inhabitants.
- The incidence rate of diagnosed pulmonary TB is on average 100/100,000 inhabitants per annum.
- Of the diagnosed TB cases, on average 50% are diagnosed as sputum-smear positive.
- The level of statistical significance is 0.05 (alpha error).
- The power for detecting an observed difference as statistically significant is 0.80 (Beta error)
- The coefficient of variation is 0.25 (for lack of situational data).
- The additional design effect due to the stepped-wedge design DEFFsw (a consequence of the imbalance between the two comparison groups except halfway the observation period) is between 1.5 and 2.0.

The number of units needed was estimated using the formula by *Hayes and Bennett* [[23]](#endnote-24)for a unmatched group-randomized trial with two arms in which the study outcome is based on disease rates [1]:

C = 1 + (zα/2+zβ)2[(λ0+λ1)/y + k2(λ02+λ12)]/(λ0-λ1)2

in which C is the number of clusters (units) in each study arm, zα/2 and zβ are the standard normal distribution vales, λ0 and λ1 are the disease rates in the baseline and the intervention arms, respectively, arm, y is the person-years in each unit, and k is the coefficient of variation. The additional design effect due to the stepped-wedge design was taken into account by inflating in this formula the standard normal distribution values of 1.96 for α=0.05 and 0.84 for β = 0.80 by multiplying these by the assumed design effect DEFFsw, as proposed by *Moulton et al*.

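### Item 4 tests rate ratios pooled over laboratories by period, which mixes the GeneXpert effect with calendar time and laboratory mix; inference should be assigned to the unit- and month-adjusted model of item 5

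*Protocol*

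**What the plan says.** Section III.10 of the Protocol lists the analyses. Item 4 obtains rates by "dividing the numbers summed over all units and strata by the summed population denominators, separately for baseline and intervention period". The rates get 95% confidence intervals. The ratios and differences between the two periods get significance tests, described only as appropriate; no test is named.

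Item 5 then fits a Poisson regression to adjust the observed rate ratios for confounding from unbalanced randomisation. Laboratory unit and month of enrolment are among its adjusters, with age, sex, treatment history and HIV status. Neither item is named as the basis for the conclusion. Details are left to a separate data analysis plan.

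Three other statements bear on this:

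- Section III.2 (Study design) justifies the stepped wedge as a way of "taking account of potential bias that would be introduced if e.g. case detection rates change over time for reasons not related to the intervention".
- Section I says: "Randomization and data analysis will not be individual, but by laboratory/PCU".
- Section III.5 (Sample size) assumes a between-unit coefficient of variation of 0.25, for want of local data.

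**The concern.** In a stepped wedge, baseline person-time comes early and intervention person-time comes late. Laboratories that switch early supply most of the intervention time, and laboratories that switch late supply most of the baseline time. Summing over laboratories within each period therefore gives a crude before-after comparison with two defects:

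- The estimate contains any change in case detection over the study months.
- Its sampling error contains laboratory differences that a Poisson calculation on the totals leaves out.

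The first defect conflicts with the reason section III.2 gives for the design. If the item 4 ratio and its test were read as the result, a trend or an unlucky switching order could be reported as an effect of GeneXpert.

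**Working it through.** **Inputs from the Protocol.** "the number of units for this study is fixed at 14"; "Units serve a population of on average 500,000 inhabitants"; baseline confirmed rate 60/100,000 per annum; k = 0.25; two-sided alpha 0.05; power 0.80; 8 months; units switch monthly in pairs. All units start in baseline and all end in intervention, so the seven pairs are taken to switch at the start of months 2 to 8.

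**The plan's own figures.** The stated formula is C = 1 + [DEFFsw × (1.96 + 0.84)]² × [(λ0+λ1)/y + k²(λ0²+λ1²)]/(λ0−λ1)², with C = 14 and y = 500,000 × half the duration in years.

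| DEFFsw | Duration | Protocol, per 100,000 | Recomputed |
|---|---|---|---|
| 1.5 | 24 months | 93 | 92.8 |
| 1.5 | 8 months | 95 | 94.5 |
| 2.0 | 24 months | 110 | 109.2 |
| 2.0 | 8 months | 112 | 111.7 |

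The inputs are therefore read as intended. At 8 months and DEFFsw 1.5, the Poisson term is (60+94.5)×10⁻⁵/166,667 = 0.93×10⁻⁸. The between-unit term is 0.0625 × (60²+94.5²)×10⁻¹⁰ = 7.83×10⁻⁸. The plan's own calculation thus puts 7.83/(7.83+0.93) = 89% of the variance between units.

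**Calendar time.** In month m, 8−m pairs are in baseline and m−1 are in intervention. Each period has 28 pair-months.

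- Mean baseline month: (7+12+15+16+15+12+7)/28 = 84/28 = 3.0.
- Mean intervention month: (2+6+12+20+30+42+56)/28 = 168/28 = 6.0.

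With no effect, a 20% rise spread evenly over the seven month-to-month intervals gives a pooled ratio of about 1.2^(3/7) = 1.08.

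**Error of the pooled log rate ratio, no effect and no trend.**

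- Cases per unit-month: 500,000 × 60/100,000 ÷ 12 = 25. Each period has 56 unit-months, so 1,400 cases.
- Poisson standard error: √(2/1,400) = 0.038.
- Intervention minus baseline months for the seven pairs: 6, 4, 2, 0, −2, −4, −6. The sum of squares over 14 units is 2 × 112 = 224.
- Laboratory-mix variance: 0.25² × 224/56² = 0.00446.
- True standard deviation: √(0.00446 + 0.00143) = 0.077.
- False-positive rate of a Poisson test: P(|Z| > 1.96 × 0.038/0.077) ≈ 33%.

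**Simulation under no effect** (gamma laboratory effects, random switching order, tests at two-sided 5%). The item 5 model was fitted to laboratory-by-month counts with laboratory, categorical month and GeneXpert terms, without the patient covariates. Trends, uneven sizes and laboratory-by-month variation are assumptions.

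| Scenario | Pooled item 4, Poisson test | Item 5, model SE | Item 5, scaled SE |
|---|---|---|---|
| k = 0, no trend | 4.7% | – | – |
| k = 0, rise of 5 / 10 / 20% over the study | 8.1 / 20.7 / 57.5% | – | – |
| k = 0.25, no trend | 33.5% | 4.3% | 5.2% |
| k = 0.25, rise of 20% | 56.0% | 5.5% | 6.0% |
| k = 0.25, uneven units (one 1.15M, two 0.2M, eleven 0.57M) | 38.4% | 5.7% | 5.7% |
| k = 0.25, extra laboratory-by-month CV 0.10 | 34.9% | 9.5% | 5.7% |
| same, CV 0.15 | 35.2% | 10.6% | 4.7% |
| same, CV 0.25 | 41.8% | 23.7% | 5.7% |

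The first two rows and the 33.5% and 56.0% use 5,000 to 20,000 runs. All other entries use 1,000 to 2,000, so differences of about one percentage point among the item 5 values are noise.

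**The case against.** The strongest reply is that item 5 already contains the right terms. Laboratory and month are both adjusters, and with the Protocol's inputs the model holds its level, even with a 20% trend or uneven unit sizes. Crude estimates followed by adjusted ones are an ordinary reporting order. Item 4 names no test, and section I says the analysis is by laboratory, which leaves room for a cluster-level method. Variance details normally belong in the data analysis plan, which is not at hand.

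Most of this stands. A reader might infer that the planned regression ignores laboratories and calendar time, or that a third of null trials would be declared positive by the analysis as a whole. The Protocol does not support either reading: the 33-34% belongs only to an ordinary Poisson test of the pooled item 4 ratio. The k of 0.25 also does not show that item 5 is anticonservative, because unit terms absorb stable differences between laboratories.

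Two things remain. A better test can repair the variance of the pooled ratio but cannot remove calendar time from its estimate; item 4 fixes that estimator rather than leaving it open. The Protocol also does not say which item governs. It gives imbalance as the reason for including month, although month is needed in a stepped wedge however well the randomisation balances.

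**Conclusion.** The point holds for item 4 and for its undefined standing against item 5. The pooled contrast is confounded with calendar time by an average of three months and should not carry a significance test. If tested with Poisson error, it has about 33-34% false positives at k = 0.25 with no trend, and 56% with an assumed 20% rise over the study. These figures rest on the Protocol's average unit size and rate, stable laboratory effects and the switching pattern above.

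Item 5 is sound on the Protocol's own inputs, at about 4-6%. The overdispersion question is secondary. The 10-24% for model-based errors requires a laboratory-by-month coefficient of variation of 0.10-0.25, which the Protocol does not give, and the analysis plan may already deal with it.

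**What to change.** 1. In item 4, present the pooled ratios and differences as descriptive, with no significance test or confidence interval on the pooled contrast.
2. State that inference rests on item 5, fitted as a Poisson model of laboratory-by-month counts with laboratory, categorical month and the GeneXpert indicator. Describe laboratory and month as design terms, not as corrections for imbalance.
3. As a low-cost safeguard, use overdispersion-scaled or negative-binomial standard errors. In the simulations, scaling brought the false-positive rate back to about 5-6%.

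City-specific month effects and a permutation check over the restricted randomisation set are optional. The change is to wording only and needs no new data. The price is somewhat wider intervals.

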## 3. Intervention

The intervention will be the introduction of the GeneXpert assay as replacement of sputum smear microscopy in routine health care settings.

During the **baseline period** all patients suspected clinically of pulmonary TB will have sputum smear examination as per routine and current NTCP guidelines, i.e. two sputum samples will be sent with a request form to the microscopy facility. The result is then communicated back to the clinic. In case of one or two positive smear examinations the patient is diagnosed with smear-positive TB and treated accordingly. In case of two negative smears the diagnosis of smear-negative TB is made or rejected on clinical grounds, generally including chest X-ray examination and an assessment of the clinical response to broad-spectrum antibiotics. Repeat smear examination may be done, as may be mycobacterial culture in case the patient qualifies the NTCP selection criteria. Since culture results may take 4 to 8 weeks, the patient may be initiated on treatment before the result becomes available if the clinical condition so requires. A negative culture result then may or may not result in discontinuation of TB treatment.

During the **intervention period** all patients suspected clinically of pulmonary TB will have sputum examination as per routine and current NTCP guidelines, but instead of microscopic smear examination of two specimens, one sputum specimen will be submitted examined using the GeneXpert (Figure 2).The result is then communicated back to the clinic. In case of a positive result the patient is diagnosed with pulmonary TB and treated accordingly. In addition, microscopic sputum smear examination will be done to classify the patient as smear-positive or smear-negative for notification purposes. Note that this will *only be done in case of a positive GeneXpert result* (i.e. for the minority of TB suspects). In case of a positive Genexpert but a negative smear examination, a second sputum specimen will be requested before treatment initiation and examined microscopically in order to fulfill the notification criteria for smear-negative TB (i.e. TB with at least two negative smears).

In case of a negative GeneXpert result but continued clinical suspicion of TB the GeneXpert can be repeated after a time period determined by the clinical condition of the patient.

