## 4. Study endpoints

The study will have the following endpoints:

1. The change in incidence rates of diagnosed and notified bacteriologically confirmed pulmonary TB comparing the baseline to the intervention period, expressed per 100,000 population per annum. We will take the rate of diagnosed TB as well as that of notified TB since the latter is restricted to patients who are put on treatment within the public health system, and data show that 10-15% of the diagnosed cases are not notified. Bacteriological confirmation will be defined as: a positive microscopic smear examination *or* a positive culture with identification positive for *M. tuberculosis,* *or* a positive MTB signal in the GeneXpert assay.
2. The change in incidence rates of diagnosed, but not bacteriologically confirmed, pulmonary TB comparing the baseline to the intervention period, expressed per 100,000 population per annum.
3. The change in incidence rates of diagnosed and notified bacteriologically confirmed (by the GeneXpert) smear-negative pulmonary TB comparing the baseline to the intervention period, expressed per 100,000 population per annum. This is the measure in which the greatest impact is expected.
4. The change in proportion of diagnosed pulmonary TB patients who are ultimately diagnosed as having MDR-TB, comparing patients enrolled in the baseline period with patients enrolled in the intervention period.

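### The MDR-TB proportion and intervals have no fixed follow-up window: crude comparisons give intervention patients 3.0 months less follow-up, and month adjustment still leaves slow detections truncated

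*Protocol*

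**What the plan says.** MDR-TB detection is the second of two objectives (Protocol, II.2). Endpoint 4 (III.4) is "The change in proportion of diagnosed pulmonary TB patients who are ultimately diagnosed as having MDR-TB", compared by period of enrolment. Section III.10 carries this through the analysis list:

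- Items 7-8: the MDR proportion per period, then crude risk ratios and differences with significance tests.
- Item 9: the same ratio from a regression adjusted for, among other things, unit and month of enrolment.
- Items 10-12: time to detection of rifampicin resistance and to second-line treatment, then crude differences with significance tests. The population is restricted to cases found: "Calculation, for patients ultimately identified with MDR-TB, of the time interval between diagnosis of pulmonary TB and detection of rifampicin resistance".
- Item 13: "Multivariate analysis of the observed differences in these time intervals using linear to adjust" for the same covariates, including month of enrolment.

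On timing of the data, III.10 says "Over the end of the observation period, data from Manaus and Rio will be extracted from SINAN and GAL". The timetable in III.6 places linkage and extraction in the three months after the observation row, with analysis starting in the last of them. No cut-off date and no minimum follow-up per patient appear. Section III.11 does not list unequal follow-up among the recognised biases.

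**The concern.** Without a window, a patient counts as having MDR-TB only if it was found before the data were pulled. In a stepped-wedge design baseline patients come early and intervention patients late, so the two groups have unequal time in which to be found.

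The diagnostic path is long enough for this to matter. On culture, III.3 says "Since culture results may take 4 to 8 weeks". The Introduction states that susceptibility testing needs culture first and that some cultures are prompted only by suspected failure at the end of the second treatment month. Under GeneXpert, a confirmed resistance signal is still referred on for culture and susceptibility testing (III.3).

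The intervals have a further problem. They exist only for cases already found, so long intervals in late enrolees are never seen. At stake are the estimates of whether GeneXpert finds more MDR-TB and finds it sooner.

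**Working it through.** **Inputs from the Protocol.** Duration: "Based on the sample size considerations above the total study duration will be 8 months" (III.6). Units: "the number of units for this study is fixed at 14" (III.5). Steps: "Therefore, they will change on a monthly basis in pairs" (III.6). Hence 7 pairs, with pair j crossing over at the start of month j+1.

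**Step 1. Reproduce the plan's figure.** In months 1 to 8 there are 7, 6, 5, 4, 3, 2, 1, 0 baseline pairs and 0, 1, 2, 3, 4, 5, 6, 7 intervention pairs. Each sums to 28, and 28/7 = 4.0 months per period. This matches the average of 4 and 4 months stated in III.5.

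**Step 2. Mean time of enrolment** (month midpoints 0.5 to 7.5; equal case load per unit and month).

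- Baseline: (7×0.5 + 6×1.5 + 5×2.5 + 4×3.5 + 3×4.5 + 2×5.5 + 1×6.5)/28 = 70/28 = 2.5 months.
- Intervention: (7×32 − 70)/28 = 154/28 = 5.5 months.
- Gap: 3.0 months.

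Mean follow-up to a common cut-off, baseline versus intervention, is 5.5 versus 2.5 months if extraction is at the end of month 8, and 8.5 versus 5.5 months if it is three months later. The gap is 3.0 in both cases. The III.6 timetable row marks only 4 observation months against the stated 8; on that reading the gap would be 3.0×4/8 = 1.5 months.

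**Step 3. Crude comparison with no true effect.** The Protocol gives no distribution for the delay from diagnosis to MDR identification, so one is assumed: log-normal, log-SD 0.5, the same in both periods. The fraction found by follow-up f is Φ(ln(f/median)/0.5), averaged over uniform enrolment within months and weighted by the pair counts above.

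| Lag after month 8 | Median delay (months) | Found, baseline | Found, intervention | MDR ratio (true 1.00) | Interval difference (true 0) |
|---|---|---|---|---|---|
| 0 | 2 | 0.921 | 0.513 | 0.56 | −9 days |
| 0 | 3 | 0.808 | 0.353 | 0.44 | −14 days |
| 0 | 4 | 0.674 | 0.240 | 0.36 | −19 days |
| 3 months | 2 | 0.994 | 0.948 | 0.95 | −4 days |
| 3 months | 3 | 0.966 | 0.824 | 0.85 | −11 days |
| 3 months | 4 | 0.906 | 0.672 | 0.74 | −18 days |

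With a 6-month lag the ratio is 0.94-1.00 and the interval bias 1-9 days. A gamma delay (shape 2, mean 2 to 6 months) gives ratios of 0.41-0.62 with no lag and 0.70-0.95 at three months.

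**Step 4. Adjusted comparison.** Patients enrolled in the same month have the same time to a common cut-off whichever period they are in. With equal delays, the within-month ratio is therefore 1.00 and the interval difference 0.

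Now let GeneXpert be faster: assumed medians 3 months (baseline) and 1 month (intervention), log-SD 0.5, equal true MDR proportions. The true mean difference is (1 − 3)×exp(0.5²/2) = −2.27 months. Within-month results:

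- No lag: MDR ratio about 1.5 instead of 1.00; interval difference −1.49 months.
- 3-month lag: MDR ratio 1.07; interval difference −1.97 months.

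With gamma delays of mean 4 and 1 months the within-month ratio is 1.73 or 1.19, and the difference is −1.17 or −2.09 months instead of −3.00.

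**The case against.** The strongest reply is that items 9 and 13 adjust for month of enrolment, which equalises follow-up between periods. This stands. The figures in step 3 belong to the crude comparisons (items 7-8 and 10-12) and not to the models. A reader might infer that the whole MDR analysis, models included, is biased one way: too few MDR cases and falsely short intervals under GeneXpert. The Protocol does not support that. In the models, if GeneXpert is faster, slow baseline detections are lost preferentially, which inflates the MDR ratio and shrinks the time gain.

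A reader might also infer one extraction date at the end of month 8. The Protocol gives an extraction period and no cut-off; the zero-lag figures are the unfavourable end, and the 3-month figures fit the timetable better. The delays are assumptions too. A median of 2 to 4 months is hard to credit for resistance detection under GeneXpert, because the assay itself reports the rifampicin signal. It is easier to credit for culture-confirmed MDR-TB or start of second-line treatment.

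Finally, the intervals are not among the four endpoints, no sample size rests on endpoint 4, and III.10 leaves details to a data analysis plan. That lowers the weight of the point but does not remove it. The open-ended endpoint, the crude tests and the linear model restricted to found cases are all fixed in the Protocol, and followed as written they give biased results.

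**Conclusion.** The point holds in limited form. The 3.0-month gap in mean follow-up follows from the design under any common cut-off, given equal case load per unit. It biases the crude MDR ratio and crude intervals. Month-of-enrolment adjustment removes the gap but not the right-truncation of slow detections, which acts differently on the two periods if their delays differ. Crude and adjusted results can therefore be biased in opposite directions, and neither is a safe check on the other.

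The sizes are conditional on the assumed delays and on the extraction lag. They are substantial if data are pulled at the end of observation, moderate at three months and small at six.

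**What to change.** Redefine endpoint 4 and items 7-13 as MDR-TB detection, and start of second-line treatment, within the same fixed window from diagnosis in both periods, for example 180 days. Extract MDR data only after that window has closed for the last enrolled patient, and state the cut-off date.

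Analyse the intervals on that equal window, or as time-to-event (cumulative incidence) among all diagnosed pulmonary TB patients, in place of linear regression among cases already found at extraction. The risk set matters: among found MDR cases nobody is censored for detection, so a survival method applied there would change nothing. The result should be described as detection within the window, not as eventual detection. Keep the adjustment for unit and month. Reconcile the 4 observation months in the timetable with the stated 8.

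Cost: one later extraction from the same two databases. A 180-day window closes about 6 months after the last enrolment, roughly 3 months beyond the extraction period in the timetable. Only the MDR results are delayed; the notification-rate endpoints can keep their schedule.
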